### Participant Inclusion Criteria

#### Cohort 1

Inclusion criteria include: 1) English-speaking; 2) pregnant women (any gestational age); 3) living in Ontario; 4) attending the Perinatal Mental Health Clinic at the recruiting hospital; 5) a history of IPV (disclosed to the PCNS during their intake assessment); and 6) symptomatology consistent with PTSD, depression, or anxiety that adheres to the diagnostic criteria outlined in the Diagnostic and Statistical Manual of Mental Disorders (DSM)-V (as assessed by the PCNS at intake).

#### Cohort 2 (Intervention and Standard Care Arms)

The inclusion criteria above apply to the intervention arm of cohort 2 as well. Additional criteria include: 1) received PCNS-delivered CBT at the Perinatal Mental Health Clinic in the past five years; and 2) at least 50% of the data required for the chart data extraction is present.

For the standard care arm, additional criteria include: 1) having received antenatal care (but not PCNS-delivered CBT) at the Perinatal Mental Health Clinic in the past five years; and 2) at least 50% of the data required for the chart data extraction is present.

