## Methods

### Design

This pilot project will consist of two cohorts: participants receiving CBT (cohort 1), as well as a retrospective chart audit of individuals who participated in the same CBT treatment within the last five years (cohort 2, intervention arm), and participants who received the accepted standard of care (cohort 2, standard care).

#### Cohort 1

A sample of 20 women currently attending the hospital-based, outpatient Perinatal Mental Health Clinic (London, Ontario, Canada) will be invited to participate in an eight-session antenatal CBT program facilitated by the clinic’s perinatal clinical nurse specialist (PCNS). CBT is currently the gold-standard approach for treating depression and anxiety. What is unique about this intervention is that it is tailored to the antenatal period and integrates attachment theory. Typically, women undergo initial screening at their pre-admission appointment for signs and symptoms of depression, anxiety, and PTSD, as well as for history of IPV. If women meet any of these criteria, they are referred for in-hospital social work or psychiatry consultations as necessary. While this intervention is currently provided to a small subset of women receiving antenatal care at the clinic, its efficacy remains untested. As such, this is considered a “specialty service” provided to identified at-risk women, and is not considered the accepted standard of care at this time.

#### Cohort 2

A retrospective medical chart review of 100 women will be conducted. All women must have received antenatal care at the recruiting hospital within the last five years and screened positive for IPV. This time frame was selected as it is representative of the duration in which the clinic’s current PCNS has been providing CBT to at-risk women. Of the 100 charts selected, 50 women must have participated in the CBT program (intervention arm), while the remaining 50 who did not will be assigned to the standard care group (these participants would have been eligible to participate but were not referred due to either lack of knowledge of the CBT program or a lack of support of the CBT program by the main health care provider). A sample size of 50 for both groups (intervention arm and standard care) will be sufficient to determine the feasibility of the study protocol for a future large-scale randomized control trial (RCT) [31].

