#### Cohort 2 (Intervention and Standard Care Arms)

Recruitment will be facilitated through the health records department at LHSC. The PCNS will identify participants who have received PCNS-delivered CBT in the last five years (intervention arm) and a general chart audit from the same time period will be used for the standard care arm. For both samples, a random sample approach will be undertaken wherein the research assistant (RA) uses a table of random numbers to select charts.

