### Power

#### Cohort 1

A sample of 20 women was selected as this is a feasibility study and it is anticipated we will reach saturation (assessed by the sole interviewer with the use of field notes) in the qualitative data [46]. This sample will be used to inform future power analysis for the large-scale RCT.

#### Cohort 2

One hundred charts will be audited (50 from each of the two arms, the intervention and standard care arms). This sample size, for this feasibility study, was selected as it will allow us to extend the breadth and depth of analysis from cohort 1. This ultimately enhances the validity of the study’s findings [31] by contextualizing the differences between the intervention and standard care, therefore contributing to valuable knowledge translation.

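### The cohort 2 standard-care arm is defined inconsistently in three places, so the CBT versus standard-care contrast would mix selection with any CBT effect

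*Protocol article*

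**What the plan says.** Protocol article, Design, Cohort 2 sets a rule for both arms: "All women must have received antenatal care at the recruiting hospital within the last five years and screened positive for IPV". Of the 50 standard-care women it adds that "these participants would have been eligible to participate but were not referred due to either lack of knowledge of the CBT program", or because the main provider did not support the program.

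Participant Inclusion Criteria, Cohort 2 says "The inclusion criteria above apply to the intervention arm of cohort 2 as well". Those carried-over criteria include "a history of IPV (disclosed to the PCNS during their intake assessment") and symptoms of PTSD, depression or anxiety to DSM criteria, both established by the perinatal clinical nurse specialist (PCNS) at intake. The CBT arm must also have "received PCNS-delivered CBT at the Perinatal Mental Health Clinic in the past five years". The standard-care arm has two additional criteria: antenatal care at the Perinatal Mental Health Clinic without CBT from the PCNS, and at least 50% of the chart data present. The base set to which these are added is not named.

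Recruitment, Cohort 2 draws the CBT arm from women identified by the PCNS, while "a general chart audit from the same time period will be used for the standard care arm". Charts are then picked by random numbers within each source.

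Statistical Analysis plans generalized estimating equations for effectiveness over time and against standard care. Cohort 2 holds the only standard-care group. According to the Abstract (Results), its data collection is finished.

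**The concern.** A comparison of treated and untreated charts can be read only if the two groups meet the same entry conditions. Here the condition being treated is written into the entry rule of one arm and left unstated for the other, and the arms come from different sources. Random selection of charts within two different sources does not make the sources alike.

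Referral is also selective by the article's own account. Design describes CBT as an extra service reaching a small part of the clinic's patients, those identified as at risk, and puts non-referral down to the provider's knowledge or attitude. Confounding by referral would remain even with identical criteria. Limitations lists small sample, single site and dependence on one therapist, but not selection between the arms. Power says cohort 2 strengthens validity by putting the differences between CBT and standard care in context, and the study is meant to inform a full-scale RCT. A contrast of unknown sign is a weak basis for that.

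**Working it through.** **1. The standard-care definitions side by side**

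| Section | Source of charts | IPV | Symptoms |
|---|---|---|---|
| Design, Cohort 2 | recruiting hospital | positive screen | implied by eligibility for CBT |
| Participant Inclusion Criteria, Cohort 2 | Perinatal Mental Health Clinic, no CBT | not stated for this arm | not stated for this arm |
| Recruitment, Cohort 2 | general chart audit | not stated | not stated |

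The CBT arm has all six cohort 1 criteria and comes from a list made by the PCNS.

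**2. Two readings**

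- Literal reading of the inclusion section: all CBT women have qualifying symptoms, and standard-care women need not.
- Charitable reading, in which eligibility in Design imports the cohort 1 criteria: IPV and symptoms are then defined by PCNS intake, and the article states no chart-based substitute for women without one.

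Neither reading assures comparable arms.

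**3. The stated sample size**

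The article says "One hundred charts will be audited (50 from each of the two arms, the intervention and standard care arms"). It justifies the number by feasibility and gives no alpha, power, effect size or SD, so there is no calculation to reproduce. For scale only, with assumed SD = 1 and two-sided alpha 0.05:

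- SE = sqrt(2/50) = 0.20.
- Difference detectable at 80% power = (1.96 + 0.84) × 0.20 = 0.56 SD.
- Power for a true 0.5 SD difference = 70.5%.

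**4. What a symptom imbalance could do (all inputs assumed)**

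Let g be the outcome gap in SD between women with and without qualifying symptoms, and p the share of standard-care charts meeting the symptom criterion (CBT arm 100%). The true CBT effect is zero, and no adjustment for symptoms is made.

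- Bias b = g × (1 − p).
- Rejection rate = Φ(b/SE − 1.96) + Φ(−b/SE − 1.96).

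| p | Bias, g = 0.5 | False-positive rate | Bias, g = 1.0 | False-positive rate |
|---|---|---|---|---|
| 100% | 0 | 5% | 0 | 5% |
| 75% | 0.125 | 10% | 0.25 | 24% |
| 50% | 0.25 | 24% | 0.50 | 71% |
| 25% | 0.375 | 47% | 0.75 | 96% |

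Example: b = 0.25 gives 0.25/0.20 = 1.25, and Φ(−0.71) + Φ(−3.21) = 0.24.

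The shift can also hide benefit. If CBT women are sicker at entry, a true 0.5 SD benefit less an opposing 0.25 SD appears as 0.25 SD and is detected 24% of the time instead of 70.5%.

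For a binary adverse outcome, the spurious risk ratio is R / (pR + 1 − p), where R is the assumed risk ratio for symptoms. With R = 1.5 and p = 0.7 it is 1.5/1.35 = 1.11; with R = 2.0 and p = 0.3 it is 2.0/1.3 = 1.54, both against CBT.

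**5. Timing**

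The added CBT criterion counts treatment received within five years and does not name the pregnancy whose birth is analysed. Even with that settled, a woman must still be pregnant to receive antenatal CBT, so very early births are less likely to enter the CBT arm. This pushes gestational age and birth weight, both abstracted, in favour of CBT, which can run opposite to the symptom shift. The sign of the net bias is therefore not known.

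**The case against.** The best defence is that the three sections are nested filters. The clinic belongs to the recruiting hospital, the general audit may be only the pool that is then screened, and eligibility in Design, together with the word for additional criteria, suggests that the cohort 1 criteria were meant for both arms. Cohort 2 is also sized for feasibility: "A sample size of 50 for both groups (intervention arm and standard care) will be sufficient to determine the feasibility of the study protocol". This stands as far as it goes. The nested reading is possible, but no section states it, and the sentence that carries the criteria over names one arm only.

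A reader might infer several stronger points that the article does not support:

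- **That the rules contradict each other outright.** They can be reconciled as filters; the fault is inconsistency.
- **That the criteria could not be met by standard-care women.** A woman can attend the clinic without receiving CBT, and Design describes pre-admission screening for depression, anxiety, PTSD and IPV, a possible chart source. What is missing is a stated way to verify them.
- **That the comparison is unadjusted.** Statistical Analysis names no covariates, but a condensed article may leave them to a fuller plan. Silence here is not a finding.
- **That CBT after birth counts as exposure.** The carried-over pregnancy criterion, and the statement that the CBT arm had the same treatment as cohort 1, point to antenatal CBT. The Abstract's broader term, perinatal, and the five-year window leave it worth spelling out.
- **That any difference would be selection alone.** It would be a mixture.

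**Conclusion.** The concern holds in this form: standard-care eligibility and source are stated inconsistently across Design, Participant Inclusion Criteria and Recruitment. As written, they permit arms that differ in the condition being treated, within the study's only contrast with standard care, and Limitations does not mention it. The document does not allow the direction or amount of bias to be calculated.

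The figures above show only that plausible imbalances are large relative to what 50 charts per arm can resolve: bias from 0.125 to 0.75 SD and false-positive rates from 10% to 96%, for g between 0.5 and 1.0 and p between 25% and 75%. None of these inputs comes from the article. Aligning the criteria brings this one source to zero; confounding by referral remains.

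**What to change.** 1. Reconcile the three sections into one eligibility rule that can be checked from charts and is applied identically to both arms: same clinic source, positive IPV screen, and documented PTSD, depression or anxiety symptoms in the index pregnancy.
2. State that CBT exposure means antenatal CBT in that index pregnancy.
3. Because abstraction is finished, restrict the abstracted charts to this rule and report the number left per arm. Data Collection says charts are not identified and will not be revisited, so where an item was not abstracted, report that the rule could not be verified.
4. In the contrast, adjust only for a small set of abstracted characteristics that precede CBT (diagnosis, obstetrical history, demographics). Do not adjust for current treatments, which may follow from CBT.
5. Report the difference as an association, and add confounding by referral to Limitations.
6. Do not interpret gestational age or birth weight differences as CBT effects. Restricting exposure to CBT before birth does not remove the timing problem.

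The cost is analysis and wording on existing data, fewer charts and wider intervals. If all 50 CBT charts stay and a share p of the standard-care charts remains, SE = sqrt(1/50 + 1/(50p)). That is 0.216, 0.245 and 0.316 for p = 75%, 50% and 25%, or intervals about 8%, 22% and 58% wider than with 50 per arm.

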### Recruitment

#### Cohort 1

Participant recruitment will be facilitated through the PCNS at the London Health Sciences Center (LHSC) in the Perinatal Mental Health Clinic. Women who are receiving antenatal care at the clinic and meet the above eligibility requirements will be provided with a business card, should they wish to learn more about the study. To mitigate any undue influence or pressure to partake in the pilot project, potential study participants will be informed that their involvement is voluntary, and their involvement with the study will have no impact on the nature or quality of care. Participants interested in the study will be asked to contact the research team, at which time the safety protocol will be enacted, and eligibility and recruitment will be completed.

#### Cohort 2 (Intervention and Standard Care Arms)

Recruitment will be facilitated through the health records department at LHSC. The PCNS will identify participants who have received PCNS-delivered CBT in the last five years (intervention arm) and a general chart audit from the same time period will be used for the standard care arm. For both samples, a random sample approach will be undertaken wherein the research assistant (RA) uses a table of random numbers to select charts.

### Safety and Security

Ensuring the physical and emotional safety of women participating in the study is of paramount importance. Upon enrollment in the study, a safety plan will be enacted, outlining secure methods of communication (via email and telephone), information storage, and an emergency protocol if contact with the participant is lost unexpectedly. This particular safety plan has been utilized successfully by both principal investigators in previous research involving survivors of IPV without any adverse events [32]. To further mitigate the risk that perpetrators of violence will discover their partner’s involvement in the study, strict privacy and confidentiality precautions will be adhered to during the transfer and storage of participants’ health information and demographic data. All personal identifiers will be removed and replaced with an encrypted identification code unique to each participant, thus ensuring anonymity. Electronic documents will be stored on the university server behind a secure firewall, while physical copies of interview transcripts and questionnaires will be stored on campus within locked research offices.

Given the sensitive and potentially triggering nature of content raised during structured in-person interviews, all study personnel will be trained to identify acute signs of distress and initiate a stress reaction protocol. This will involve the immediate discontinuation of the interview, followed by referrals to appropriate crisis stabilization and treatment interventions if needed, including the 24-hour helpline for abused women. All participants will be offered a handout describing the signs and symptoms of stress reaction along with various community resources capable of providing comprehensive mental health support.

Finally, should a participant disclose suicidal ideation—whether shared with the PCNS or RA directly, or flagged as high risk (indicated by an affirmative response to questions of self-harm) when completing the Edinburgh Postnatal Depression Scale (EPDS)—they will be immediately referred to the London-Middlesex Suicide Prevention Council Support Line by the individual, or through automatic prompt via the online questionnaire. If it is suspected that juvenile dependents of study participants are experiencing abuse or neglect, members of the research team will report the need for protection to the Children’s Aid Society, as per regulation set forth by the Child and Family Services Act (1990).

### Data Collection

Data collection will occur simultaneously for both cohorts.

#### Cohort 1

Data collection will occur at baseline (T1; prior to the PCNS-delivered CBT and during pregnancy), two (T2), six (T3), and twelve (T4) months postpartum. At T1 and T2, a mixed-method data collection model will be utilized wherein women will complete a semistructured interview for approximately one hour (audio-recorded) and complete a short demographic survey. At T3 and T4, participants will be sent an electronic link to complete a questionnaire (or alternatively, if this is thought to be unsafe, a member of the research team will meet with the participant to complete a hardcopy version).

During the T1 data collection interaction, the study protocol will be thoroughly described and consent to participate will be obtained. Throughout the data collection period (T1-T4), a detailed safety plan will be reviewed (updated as needed), and participants will be provided a $25 honorarium (retail gift card) in recognition of their contribution to the study. To further reduce potential barriers to involvement, those in need of reimbursement for childcare or transportation expenses to attend the in-person interviews will be offered $15 and $10, respectively.

#### Cohort 2

A data abstraction instrument (developed by the co-principal investigators) will be used to collect data. Data will be pulled from multiple sources including: the e-chart, nursing chart, paper chart, and nursing care plan. Maternal data extraction will include: a) scope of mental illness, including diagnosis and current treatments; b) general physical and mental health status; c) obstetrical history; d) birth summary; e) care plan, including CBT interventions; f) evidence of learned CBT strategies or alternative coping strategies used during birth; g) birth experience; h) evidence of maternal-infant attachment; and i) demographics. Conversely, data extraction for infants at the time of parturition will include: a) gestational age; b) weight; c) length; d) head circumference; e) complications and interventions; f) Appearance, Pulse, Grimace, Activity, and Respiration (Apgar) score; and g) newborn physical exam. The chart review will take place at the recruiting hospital and does not require any patient contact. No identifying information will be collected, as the audit will be conducted for each chart in its entirety during a single data extraction period, thereby eliminating the need to refer back to any particular patient’s chart.

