### Statistical Analysis

For quantitative data, the overall impact of the PCNS-facilitated CBT intervention will be assessed using generalized estimating equations [41] to determine the effectiveness over time, and in contrast to standard care. Descriptive statistics, including measures of central tendency and dispersion, will be computed for all continuous variables and frequency tables will be constructed for all categorical variables.

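### In cohort 2 the contrast with standard care on attachment and coping can rest only on two chart items: one partly measures CBT exposure, the other depends on what clinicians recorded

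*Protocol article*

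**What the plan says.** **The contrast.** Statistical Analysis says generalized estimating equations will be used "to determine the effectiveness over time, and in contrast to standard care". The Power section gives cohort 2, with 50 charts per arm, the task of "contextualizing the differences between the intervention and standard care". The Abstract counts improved attachment and coping among the markers of efficacy, and attachment is the fourth of the five objectives.

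**The data.** Under Data Collection, Cohort 2, coping (item f) and attachment (item h) enter in this part of the extraction list: "evidence of learned CBT strategies or alternative coping strategies used during birth; g) birth experience; h) evidence of maternal-infant attachment". The sources are "the e-chart, nursing chart, paper chart, and nursing care plan". The same list includes the care plan with its CBT interventions. Each chart is read completely in one session, without contact with the woman.

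**The arms.** Under Design, the CBT programme is described as building in attachment theory. Standard-care women were eligible but not referred, because the programme was not known or the main provider did not support it.

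**The concern.** Attachment and coping have their own questionnaires under Outcome Measures (MAI and PCI). Neither appears in the chart extraction list, and a retrospective audit without patient contact cannot administer them. Cohort 1 has the questionnaires but no comparator. On this text, any comparison with standard care on attachment or coping has to use the two chart items.

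Both are weak for that purpose. The coping item contains a component that follows from having received the intervention. The attachment item measures attachment and note-writing together, and there are reasons to expect note-writing to differ: the programme's content, the providers' attitude to it, and an abstractor who can see the arm.

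At stake is whether a documentation difference is reported as better attachment or coping after CBT. The Conclusions section links confirmed hypotheses to scale-up of the intervention.

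**Working it through.** The article gives no effect size, alpha or power for cohort 2; 50 per arm is justified on feasibility grounds. There is no figure of the plan's own to reproduce. Apart from the 50 charts per arm, every rate below is an assumption. The test is a two-sided 5% pooled z-test, with exact binomial rejection probabilities.

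**Step 1. Coping item (f).** Let *a* be the chance that alternative coping is recorded, the same in both arms. Let *c* be the chance that a CBT strategy is recorded, possible only in the CBT arm and independent of *a*.

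- Standard care meets the item with probability *a*.
- The CBT arm meets it with probability 1 − (1 − *a*)(1 − *c*).
- The gap is *c*(1 − *a*).

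With *c* = 0.30:

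| *a* | CBT arm | Standard care | Gap | Significant, favouring CBT |
|---|---|---|---|---|
| 0 | 0.30 | 0 | 30 points | nearly 100% |
| 0.4 | 0.58 | 0.40 | 18 points | 46% |
| 0.8 | 0.86 | 0.80 | 6 points | 13% |

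If CBT strategies merely replace other coping, the gap is 0. The item is pure exposure only in the first row. In the other two rows it mixes exposure with coping.

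**Step 2. Attachment item (h).** Let *p* be the true proportion with attachment, equal in both arms, and let dC and dS be the chances that it is recorded in the CBT and standard-care arms. A silent chart counts as showing no evidence; this too is an assumption. The recorded proportions are *p*·dC and *p*·dS, and the apparent effect is *p*(dC − dS) although the true effect is zero.

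| dC vs dS | Apparent gap, *p* = 0.6 / 0.8 | Significant, favouring CBT, *p* = 0.6 / 0.8 |
|---|---|---|
| 0.7 vs 0.7 | 0 / 0 | 2.7% / 2.8% |
| 0.8 vs 0.7 | 6 / 8 points | 9.5% / 13.1% |
| 0.8 vs 0.6 | 12 / 16 points | 23.9% / 38.2% |
| 0.9 vs 0.6 | 18 / 24 points | 46.2% / 70.4% |
| 0.6 vs 0.8 | −12 / −16 points | 0.1% / 0.0% (favouring standard care 23.9% / 38.2%) |

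Check of one cell by normal approximation (*p* = 0.6, 0.8 vs 0.6):

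- The recorded proportions are 0.48 and 0.36, with mean 0.42.
- Pooled SE = √(0.42 × 0.58 × 2/50) = 0.0987, so the critical difference is 1.96 × 0.0987 = 0.193.
- Unpooled SE = √(0.48 × 0.52/50 + 0.36 × 0.64/50) = 0.0980.
- P(Z > (0.193 − 0.12)/0.0980) = P(Z > 0.75) = 0.23, close to the exact 0.239.

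**Step 3. Direction.** The text gives grounds for expecting more attachment notes in the CBT arm: attachment is part of the programme (Design), and the effect of trauma on attachment is one of its five core components (Feasibility). Nothing in the text fixes the direction. The last row shows the bias reversing.

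**The case against.** The other side has several fair points.

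- **The contrast on these items is inferred.** Data Collection lists extraction fields. Statistical Analysis does not say which variables enter the comparison, and the Power section speaks only of contextualizing. This stands as a limit on the point. But the Abstract names attachment and coping as efficacy criteria, and no other data on them exist for standard care.
- **The abstraction instrument is not shown.** It may define both items and separate silence from absence. No passage says that silence is coded as absence, and leaving such rules out of an article is no fault. Even so, an instrument cannot equalize what clinicians wrote, or open a CBT-only component to women without CBT.
- **A reader might infer that the comparison favours CBT by design.** The documents do not support that. The coping item also counts alternative strategies, which standard-care women can show. No passage says that staff wrote more about CBT women, and both arms come from the same clinic. Fuller notes could also record more attachment problems.
- **A reader might also infer that the entry rule, "at least 50% of the data required for the chart data extraction is present", is stricter for standard-care charts.** The same rule applies to both arms. The care-plan and coping groups can be filled in the chart of a woman without CBT, so this does not follow.

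**Conclusion.** The point holds in a limited form. If cohort 2 is used to compare attachment or coping with standard care, the pooled coping item partly measures exposure, and the attachment item can turn a difference in recording into an apparent effect.

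For attachment, a 20-point recording gap (0.8 vs 0.6) raises the chance of a false result favouring CBT from about 3% to about 24-38%. This assumes equal true attachment in 60-80% of women, silent charts counted as no evidence, and a two-sided 5% test with 50 per arm. A 10-point gap (0.8 vs 0.7) gives about 10-13%. A bias towards CBT is the more plausible direction, but it is not established. For coping, the size depends on how often other strategies are recorded and whether CBT strategies add to them or replace them.

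These figures show scale only; they do not estimate the bias in this study. The point warrants a low-cost change in analysis and reporting.

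**What to change.** 1. Split the coping item. Report use of CBT strategies as uptake within the CBT arm only, and do not use the pooled item as a between-arm outcome.
2. For attachment and for coping other than CBT strategies, keep not documented apart from documented absence or concern where the abstracted data allow, and report documentation rates by arm. Where the data do not allow it, say so.
3. Present the cohort 2 contrast on attachment and coping as descriptive, not as evidence of effect.

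**Cost.** The Abstract says that cohort 2 collection is finished, and Data Collection says that charts cannot be traced back. Masking the abstractor or re-reading charts is therefore no longer open for this sample. The three steps use data already abstracted and need no new staff or chart access. Step 2 may be only partly possible, depending on how silence was entered; step 3 applies either way. The price is that cohort 2 no longer supports an effect claim on attachment or coping.

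### Cohort 2 arms are set in retrospect by receipt of antenatal CBT with no common start of follow-up, so any contrast of gestational age and related infant outcomes can tilt towards CBT, by an amount that depends on an unstated CBT start time

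*Protocol article*

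**What the plan says.** Cohort 2 is a review of 100 charts, 50 per arm. The Design section sets the arms by what happened later in the pregnancy: half of the charts are those of women who "participated in the CBT program (intervention arm), while the remaining 50 who did not will be assigned to the standard care group". The inclusion criteria repeat this. The CBT arm must have "received PCNS-delivered CBT at the Perinatal Mental Health Clinic in the past five years". The standard-care arm is defined by "having received antenatal care (but not PCNS-delivered CBT) at the Perinatal Mental Health Clinic in the past five years".

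The cohort 1 criteria carry over to the CBT arm of cohort 2, including "pregnant women (any gestational age" and no upper limit. The treatment is described as "an eight-session antenatal CBT program". Neither the interval between sessions nor the week of starting is given.

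Under Recruitment, "a general chart audit from the same time period will be used for the standard care arm", with charts drawn by random numbers. Design adds that the standard-care women would have been "eligible to participate but were not referred due to either lack of knowledge of the CBT program or a lack of support" by the main provider.

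Under Data Collection, cohort 2, "data extraction for infants at the time of parturition will include: a) gestational age", then the other newborn measures. The first goal under Objectives covers child health as well as maternal outcomes, the Discussion hypothesises better child health after birth, and Statistical Analysis sets CBT against standard care. Only cohort 2 has a standard-care arm.

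**The concern.** Receiving antenatal CBT takes time spent still pregnant. A pregnancy that ends before the first session is excluded from the CBT arm by definition. The rules for standard care contain no matching requirement: antenatal care without CBT is enough, however early the delivery. This is immortal-time bias. It bears directly on gestational age, and through it on weight, length, head circumference, Apgar score and complications.

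At stake is the infant part of the only controlled contrast in the study. The bias can make infant outcomes look better after CBT when CBT does nothing. The protocol's conclusions link positive findings to adoption and scale-up.

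**Working it through.** The plan gives no figure for this point to reproduce. The cohort 2 size is consistent (50 + 50 = 100) but comes without alpha, power, effect size or preterm rate. The check is therefore a calculation under no CBT effect, with stated assumptions.

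**Inputs from the protocol:** arms by receipt of CBT; entry at any gestational age; no gestational-age requirement for standard care; 50 charts per arm.

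**Assumptions, not in the protocol:** preterm rate p of 8%, 15% or 20%. Preterm births are split 6% at 22–27 weeks, 10% at 28–31, 12% at 32–33 and 72% at 34–36. Standard-care women enter at weeks 8–20. The gestational-age distribution is identical in both arms (2,000,000 simulated pregnancies per preterm rate).

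**Formula.** Let e be the share of pregnancies that end before the CBT entry point. The earliest assumed birth is after the latest standard-care entry, so no standard-care chart is lost. All births lost from the CBT arm are preterm. The null preterm risk ratio is

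RR = (p − e) / [p × (1 − e)].

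Example: start uniform over weeks 20–36, p = 0.20, e = 0.026. RR = 0.174 / (0.20 × 0.974) = 0.174 / 0.1948 = 0.89.

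| Entry to CBT arm (assumed) | e at p = 8 / 15 / 20% | RR at p = 8 / 15 / 20% | Mean gestation, CBT minus standard care (weeks) |
|---|---|---|---|
| First session, weeks 12–24 | 0.000 / 0.000 / 0.000 | 1.00 / 1.00 / 1.00 | 0.00 / 0.00 / 0.00 |
| First session, weeks 12–34 | 0.004 / 0.007 / 0.010 | 0.96 / 0.96 / 0.96 | 0.04 / 0.08 / 0.10 |
| First session, weeks 20–36 | 0.011 / 0.020 / 0.026 | 0.88 / 0.89 / 0.89 | 0.10 / 0.18 / 0.23 |
| All 8 weekly sessions, start weeks 12–28 | 0.007 / 0.014 / 0.018 | 0.92 / 0.92 / 0.93 | 0.08 / 0.14 / 0.18 |
| All 8 weekly sessions, start weeks 20–30 | 0.023 / 0.043 / 0.057 | 0.73 / 0.75 / 0.76 | 0.18 / 0.32 / 0.42 |

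**A second set of assumptions.** With 10% preterm, clinic intake uniform over weeks 10–34 or 16–34, standard care followed from intake and the first session 2 to 4 weeks later, RR is 0.86 to 0.96. Using the gestational-age distribution of the table instead gives 0.84 to 0.96. If the arm is read as completers of eight weekly sessions, the same setting gives 0.71 to 0.82.

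**In charts.** With first sessions at weeks 20–36 and p = 20%, the expected preterm births per 50 are 50 × 0.200 = 10.0 under standard care and 50 × 0.178 = 8.9 under CBT. At p = 8% they are 4.0 and 50 × 0.070 = 3.5.

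**False positives.** A t test on gestational age with 50 per arm, nominal 5%, rejects about 5–7% of the time in most scenarios. The exception is completers starting at weeks 20–30, at 6–13%.

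**Check of the remedy.** Holding standard care to the same gestational-age landmark returns RR 1.00 and a mean difference within 0.001 weeks in every scenario.

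**The case against.** Several points on the other side are sound.

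- **The comparison is inferred.** Data Collection only lists what is abstracted. The five objectives and the Outcome Measures section name no infant birth measure. The inference from the goals, the Discussion and Statistical Analysis is fair, but a reader should not take a planned test of gestational age as stated fact.
- **Early delivery as such does not bar entry.** A reader might infer that women who deliver early cannot be in the CBT arm. Only delivery before CBT starts keeps a woman out. Under the assumed distribution most preterm births fall at 34–36 weeks, and many of those women could already have started.
- **Ratios of 0.7 to 0.8 need a completers-only arm.** The protocol speaks of participating in or receiving CBT, not of completing it, and gives no weekly schedule. Those ratios are a hypothetical worst case.
- **Non-referral mitigates in part.** Because controls are described as eligible but not referred for provider reasons, a woman who was referred and delivered before session one should not become a control. This does not require controls to be undelivered at a comparable CBT start, and neither the inclusion criteria nor the recruitment rule shows how it is applied.
- **An article may leave an index date to the full protocol.** That is true, and the missing date alone would not be a finding. The point rests on the arm definitions that the article does state, which create the imbalance unless something corrects it.

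**Conclusion.** The concern holds in a limited form. The stated arm rules allow immortal-time bias in gestational age and the infant measures that depend on it, and any bias from this mechanism favours CBT. It matters only if those measures are contrasted between arms, as the protocol implies.

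Read literally, with the arm meaning women who received CBT, the null preterm risk ratio is about 1.00 for starts at weeks 12–24 and about 0.86 to 0.96 for later starts. The lower end moves by about 0.02 with the assumed distribution of preterm births. Preterm rates, session timing and intake timing are all assumptions. The documents therefore do not support saying that CBT will look protective, only that it may.

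With 50 charts per arm the shift is about one preterm birth or less on this reading, and the false-positive rate is barely raised. The harm is a tilted estimate rather than a likely false significant result. The maternal mental health and attachment outcomes are not tied to this mechanism in the same direct way. The point deserves correction because the tilt runs in a known direction and can be reduced at small cost.

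**What to change.** 1. Define CBT exposure in cohort 2 as at least one session, not completion of the programme.
2. Check whether gestational age at the first session was abstracted. The abstraction list names the care plan including CBT interventions but no session date. The abstract says cohort 2 data collection is finished, and the article says no identifiers are kept and charts are not revisited, so this item may not be recoverable.
3. If it was abstracted, compare each CBT chart only with standard-care pregnancies still ongoing at that gestation, by a matched landmark or a model with delayed entry.
4. If it was not, report gestational age and the infant outcomes that depend on it descriptively by arm, make no effect claim, and state this bias as a limitation. This should be the default whenever the first-session gestation is missing.
5. State how non-referral was established for standard-care charts.

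The cost is analysis and reporting work. A few early-delivering standard-care charts leave the comparison, or the infant contrast becomes descriptive only.
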